### Selection criteria

The study will involve adults who have been previously diagnosed with T2D by their treating physician, with A1c > 7% and < 13%, with and without pharmacological treatment for diabetes (hypoglycemic agents or insulin). Participants >65 years old with ≤10 years of diabetes diagnosis

Participants with severe complications of the disease (chronic renal failure, blindness, or amputation), requiring specialized medical and nutritional care will be excluded as well as people with morbid obesity (BMI ≥ 35 kg/m^2^). Selection criteria for the study are described in Figure 1.

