### Results of the study

Primary objective. To evaluate the effect on metabolic control through the measurement of A1c levels and fasting glucose before and after 12 months of intervention. The measurement will be considered a continuous variable to identify achievement in metabolic control from A1c (≤7%). Secondary objectives. To assess changes in lipid profile (total cholesterol, LDL-c, HDL-c, and triglycerides), and body composition (weight, BMI, fat percentage, fat mass, and waist circumference. After the intervention, it will be possible to compare the clinically significant results of the metabolic variables in control targets: HbA1c % (≤7%), fasting glucose mg/dl (≤130), cholesterol mg/dl (≤200), LDL-cholesterol mg/dl (≤100), HDL-cholesterol mg/dl (≥40 men and ≥50 women) and triglycerides mg/dl (≤150).

The assessment of lifestyle through IMEVID, validated in the population with diabetes in Mexico, will be treated as a categorical variable, ranging from adequate and regular to inadequate lifestyle. Quality of life will be assessed through Diabetes-39, which includes different components of quality of life and will be analyzed as a categorical variable.

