### Statistical analysis

Descriptive statistics will be used with measures of central tendency and dispersion for quantitative variables that have a parametric distribution; variables with free distribution will be reported in median and interquartile range and will be presented in summary measurement tables. One-way ANOVA or Kruskal Wallis test will be used to compare the effect on clinical, anthropometric, and biochemical variables between groups. An X^2^ test will be used to evaluate the effect of the intervention between groups for metabolic control goals. An intention-to-treat analysis will be performed for the three groups in the clinical trial. In addition, a per-protocol analysis will be performed on the outcome variables according to compliance with the interventions. To this end, the level of compliance with the educational modules will be measured, as well as the use of the mobile application. A repeated measures ANOVA test will also be performed to analyze the effect of the intervention in each of the groups. A logistic regression model will be used to identify the effect of the intervention on the primary target variable, A1c, as a dichotomous variable in glycemic control and uncontrol. It will be adjusted for other variables, such as intervention group, years of diagnosis, physical exercise, schooling, marital status, and occupation.

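### For glucose and the four lipid targets, 12-month control status mixes patients who reached target with patients already there, and the planned chi-square is valid but wastes the baseline values (minor)

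*Protocol article*

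**What the plan says.** Results of the study sets absolute cut-offs for six variables and reads them at the end: "After the intervention, it will be possible to compare the clinically significant results of the metabolic variables in control targets". Besides A1c ≤7%, the list is "fasting glucose mg/dl (≤130), cholesterol mg/dl (≤200), LDL-cholesterol mg/dl (≤100"), and "HDL-cholesterol mg/dl (≥40 men and ≥50 women) and triglycerides mg/dl (≤150"). No cut-off carries a condition on where the patient started.

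Statistical analysis names the test for these goals: an X² "test will be used to evaluate the effect of the intervention between groups for metabolic control goals". The only adjusted binary model is reserved for A1c: "A logistic regression model will be used to identify the effect of the intervention on the primary target variable, A1c". The covariates it gives as examples include no baseline laboratory value.

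Selection criteria admits patients "with A1c > 7% and < 13%, with and without pharmacological treatment for diabetes". The exclusions in the text concern severe complications and BMI of 35 kg/m² or more; none refers to glucose or lipids. Table 1 schedules glucose and the lipids at baseline and at 12 months.

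**The concern.** Everyone enters with A1c above 7%, so an A1c of 7% or less at 12 months means that the target was reached. For the other five variables the same yes/no means reached or never left. A patient whose LDL goes from 85 to 90 mg/dl is at target; one who falls from 190 to 105 is not. Set side by side in one table, the six rows look alike but measure different things.

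Two things are at stake. One is interpretation: the five proportions could be read as attainment on a par with A1c. The other is efficiency: a patient's 12-month status depends strongly on the starting value, and a test of arm by status cannot use it. Most of these endpoints are secondary, although Results of the study also places fasting glucose in the primary objective.

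**Working it through.** **The plan's own figure.** The sample size in Design and setting reproduces: 2 × (1.96 + 0.84)² × 1.3² / 0.5² = 105.997, so 106 per group; 106 / 0.8 = 132.5, so 133; raised to 136, and 3 × 136 = 408. This covers mean A1c only. The plan gives no figure for the control targets. After 20% loss, 136 × 0.8 = 108.8, so 108 or 109 per arm is used below.

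**Assumptions.** The plan gives no baseline lipid distribution and no lipid effect size, so all of the following are assumed: LDL normal with mean 100, 110 or 125 mg/dl and SD 35, correlation between baseline and 12 months 0.5 to 0.7, an effect of 10 or 15 mg/dl for every treated patient, target ≤100, two arms of 108, two-sided 5%.

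**Share at target at entry.** Φ((100 − mean)/35): mean 100 gives 50%; mean 110 gives Φ(−0.286) = 39%; mean 125 gives Φ(−0.714) = 24%. At mean 110, 55-65% of those at target at 12 months were already there at entry.

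**Simulated power over the three means:**

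| Comparison | 10 mg/dl | 15 mg/dl |
|---|---|---|
| Unadjusted chi-square on status | 35-38% | 66-71% |
| Logistic on arm and baseline LDL | 41-54% | 72-86% |
| Unadjusted comparison of 12-month means | 54-56% | 87-89% |

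With no effect, the chi-square and the logistic model both reject in about 5% of trials. Setting by setting, the logistic gain was about 3 to 18 points across repeated runs. With 1,500 trials the simulation error near 50% is √(0.5 × 0.5 / 1,500) = 1.3 points, so small differences between runs carry no meaning.

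**How much is due to patients already at target?** In the same model, enrolling only off-target patients at the same n moved chi-square power from 39% to 42% (r = 0.5) and from 38% to 46% (r = 0.7) for 10 mg/dl, and from 73% to 73% and from 71% to 82% for 15 mg/dl. That is 0 to 11 points. With off-target entry only and r = 0.7, the logistic model still led by about 6 points, which is general covariate precision.

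**A second model, in which the intervention acts only on off-target patients.** Assume 109 per arm, a share q at target at entry, 85% of these still at target at 12 months in both arms, and 20% against 40% of off-target patients reaching target. The 12-month proportions are 0.85q + 0.20(1 − q) and 0.85q + 0.40(1 − q), so the difference is 0.20(1 − q).

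| q | Difference (points) | Power, planned test (two arms) | Power, stratified by baseline status |
|---|---|---|---|
| 0 | 20 | 90% | 90% |
| 0.2 | 16 | 67% | 77% |
| 0.4 | 12 | 42% | 56% |
| 0.6 | 8 | 23% | 31% |
| 0.8 | 4 | 10% | 12% |

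The type I error of the three-arm chi-square, simulated under this model, was 5.0%, 5.2% and 5.0% at q = 0, 0.4 and 0.8.

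**The case against.** The strongest reply is that nothing is wrong with the test. Randomization spreads patients already at target evenly in expectation, and the proportion at target at 12 months, including those kept there, is a legitimate endpoint. This stands. A reader might infer that the patient going from 85 to 90 is credited to the intervention, or that the comparison is biased. Neither follows: such patients count in every arm, only the difference between arms is attributed to treatment, and the simulated error rate stays at 5%.

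Second, a reader might infer that real lipid effects will be missed. The document does not support that. It also plans one-way ANOVA or Kruskal-Wallis on the biochemical variables, and a repeated-measures ANOVA. In the LDL model, a plain comparison of 12-month means is at least as powerful as the adjusted logistic model, and the fall from 190 to 105 counts in full. This stands too, and it is why the point is minor. It does not repair the target comparison itself.

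Third, the protocol speaks of achievement for A1c only; for the other variables it speaks of targets and goals. So the document does not itself claim attainment for lipids or glucose, and the point on wording is a precaution for reporting.

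Last, baseline covariates for supplementary binary endpoints are often left to an analysis plan, which is not shown. Here, however, the article names the cut-offs and the test, so this is a stated choice that can be improved.

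**Conclusion.** The point holds as a minor matter of efficiency and labelling, not of validity. For five of the six targets, 12-month status mixes reaching with remaining, and the stated test ignores a baseline value that the trial will hold. Under the assumed LDL values, adjustment raises power from about 35-38% to 41-54% for 10 mg/dl and from 66-71% to 72-86% for 15 mg/dl. Only part of this is due to patients already at target. The larger losses in the second model require that the intervention acts only on off-target patients, which the document does not say.

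The conclusion rests on the text of Selection criteria, since Figure 1 is not shown. The sizes rest on assumed LDL figures and pairwise comparisons; nothing comparable was computed for glucose, total cholesterol, HDL or triglycerides.

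**What to change.** For fasting glucose, total cholesterol, LDL, HDL and triglycerides, replace the unadjusted chi-square by logistic regression of at-target status at 12 months on arm and the baseline value of the same variable, keeping all randomized patients in the comparison. Because the HDL cut-off differs by sex, add sex to that model.

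Add one table by arm: newly at target among those off target at entry, and lost target among those at target at entry. Describe the overall proportion as at target at 12 months, not as attainment comparable with the A1c target. Do not restrict the main comparison to patients off target at entry; that drops patients and ignores any effect on staying at target.

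The cost is a change of analysis wording and one extra table, with no new data. The model gives a conditional odds ratio in place of a simple difference in proportions, and the difference can be reported beside it.

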### Group with educational website program

Participants will receive the educational intervention with the website called “I Understand my diabetes”, designed by a group of clinical experts in diabetes, including physicians, nutritionists, diabetes educators, and epidemiologists. This educational site was previously validated through expert consensus and usability testing in individuals with type 2 diabetes (17, 28). The content, images, videos, and exposure time were previously validated through expert consensus, along with the usability, comprehensibility, and perceived usefulness among individuals with diabetes from the clinics where the intervention will be implemented. The educational course is available on the Moodle platform at https://entiendomidiabetes.org/.

The intervention includes ten interactive modules on topics such as diabetes education, pharmacological treatment, glycemic control indicators, nutrition, myths and facts about diabetes, complications, depression, and family support. Each module integrates visual aids, concise text, and videos to facilitate comprehension. Interactive activities within each module are designed to reinforce learning and promote active self-management of type 2 diabetes (T2D).

Participants will review one module per week, completing all modules in an organized manner over a two-month period. Thereafter, unrestricted access to the modules will remain available, allowing participants to revisit those of preference during the study follow-up period. At each in-person visit, emphasis will be placed on the modules reviewed and any questions regarding their content will be addressed. In addition, participants will receive a dietary plan tailored to their current weight and comorbidities, along with prototype menus to support dietary adherence. Upon completion of all modules, participants will be awarded a certificate of completion.

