### Group with usual care

Participants in the control group will receive general nutritional recommendations for following a healthy diet, as well as general measures for diabetes care. General physical activity recommendations will follow national diabetes care guidelines. In order to minimize follow-up losses, a communication link will be established with each participant's primary care provider, who will encourage continued participation. Appointments will be scheduled flexibly, and participants will receive reminders through the mobile app and follow-up calls.

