**Figure 5 F5:**
[figure not shown]
Follow-up and procedures.

**Primary measurements**: A1c (Basal and 12 months).

**Secondary measurements**: Lipid profile. Anthropometry and body composition. Lifestyle. Quality of Life. Physical Activity Level. (Basal and 12 months). Medical and Nutritional Therapy. In the baseline phase, participants will receive a complete plan that will include dietary and physical exercise recommendations, together with the collection of sociodemographic, clinical and biochemical data. Blood pressure will be taken, and relevant questionnaires will be administered. At 12 months, biochemical and anthropometric data will be reevaluated, and appropriate instruments will be applied. Follow-up visits will be scheduled at 3 and 6 months to reinforce medical and nutritional interventions.

At baseline, a comprehensive assessment will be conducted, including dietary and physical activity recommendations, collection of sociodemographic, clinical and biochemical data, blood pressure measurements and administration of standardized questionnaires. These evaluations will be repeated at 6 and 12 months. Additional follow-up visits at months 3 and 6 will reinforce interventions. Visit time points and assessments are summarized in Table 1.

**Table 1 T1:** Schedule of assessments.

Measurements during the intervention		Months			
	Basal	3	6	9	12
Medical examination to obtain sociodemographic and clinical data, measurement of systolic and diastolic blood pressure	X				
Biochemical data in blood samples (A1c, glucose, serum creatinine, total cholesterol, triglycerides, LDL-c and HDL-c).	X				X
Measurements of body weight, height, waist circumference, fat percentage, fat mass and lean mass	X	X		X	X
Medical and nutritional therapy, 24 h food reminder record.	X	X		X	X
Lifestyle (IMEVID), Quality of Life (Diabetes 39) Physical Activity Level (IPAQ)	X		X		X
Creation of users to the educational website and/or mobile App	X^a^				
Telephone call to reinforce the intervention group			X		

a For groups with educational website and mobile app + educational website.

The inclusion and follow-up of participants in the study is shown in Figure 6. The study follows the Standard Protocol Elements for Randomized Clinical Trials guidelines.

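### The per-protocol analysis rests on compliance measures that exist only in the two digital arms, so it can show a benefit over usual care without any true effect

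*Protocol article*

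**What the plan says.** The Statistical analysis section of the protocol article first states that "An intention-to-treat analysis will be performed for the three groups in the clinical trial". It then adds that "a per-protocol analysis will be performed on the outcome variables according to compliance with the interventions", and says how this will be done: "the level of compliance with the educational modules will be measured, as well as the use of the mobile application". No other compliance measure is named, and none is given for usual care.

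The Table 1 footnote under Follow-up and procedures limits the creation of website and app users: "For groups with educational website and mobile app + educational website". The usual-care section describes advice only: "Participants in the control group will receive general nutritional recommendations for following a healthy diet, as well as general measures for diabetes care".

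The between-group method for continuous outcomes has no covariates: "One-way ANOVA or Kruskal Wallis test will be used to compare the effect on clinical, anthropometric, and biochemical variables between groups". Control targets are compared by chi-square. The only covariate list belongs to the logistic model for glycaemic control and is not tied to the per-protocol set.

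**The concern.** A criterion built on modules and app use can remove participants from the digital arms but not from usual care. Whatever cut-off is chosen, selection is one-sided. The digital arms keep their engaged members, while usual care keeps everyone, including those who would not have engaged if offered the tools.

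Engagement is plausibly related to prognosis here. The Discussion itself names socioeconomic and cultural barriers to using technology in care. One of the outcomes, IMEVID, scores treatment compliance and diabetes information, which are close to engagement itself.

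The web versus web + app contrast may also be affected. App use can be required in only one of those arms, so their per-protocol sets may be selected differently.

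At stake is the reading of a per-protocol result reported next to intention-to-treat: a difference in its favour could reflect who was kept rather than what was delivered.

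**Working it through.** **The plan's own figure.** Design and setting gives SD 1.3, difference 0.5, two-sided alpha 0.05 and 80% power. Then 2 × (1.96 + 0.84)² × 1.3² / 0.5² = 2 × 7.84 × 1.69 / 0.25 = 105.997, so 106 per group. With 20% loss, 106 / 0.8 = 132.5, so 133; the plan recruits 136, and 3 × 136 = 408. The sample size reproduces and is not in question. The protocol gives no figure for the per-protocol analysis.

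**Inputs for the check**
- Completers per arm: 136 × 0.8 = 108.8, taken as 108.
- SD 1.3, from the plan.
- Compliance share c = 0.6 or 0.5: assumption.
- Prognostic gap d = 0.3 or 0.5 points, by which compliers' A1c would be lower than non-compliers' without any intervention: assumption.
- True treatment effect zero.

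**Bias.** The arm mean is c × (complier mean) + (1 − c) × (non-complier mean). Compliers therefore lie (1 − c) × d below the mean of their whole arm, and so below unselected usual care.

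**Type I error.** SE = 1.3 × √(1/(108c) + 1/108). With z = bias / SE, the rejection probability is P(Z > 1.96 − z) + P(Z < −1.96 − z).

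| c | d | Bias | SE | z | Type I error |
|---|---|---|---|---|---|
| 0.6 | 0.3 | 0.12 | 0.204 | 0.59 | 9.0% |
| 0.6 | 0.5 | 0.20 | 0.204 | 0.98 | 16.5% |
| 0.5 | 0.3 | 0.15 | 0.217 | 0.69 | 10.6% |
| 0.5 | 0.5 | 0.25 | 0.217 | 1.15 | 21.1% |

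The bias is 24% to 50% of the 0.5 point target (0.12 / 0.5 and 0.25 / 0.5). With d = 0 it is zero and the error returns to 5%.

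**Cross-check with the planned three-arm ANOVA.** A null simulation used 109 completers per arm, 4,000 runs per scenario, and a latent propensity to comply with correlation rho to lower 12-month A1c. Compliers alone were kept in the two digital arms and everyone was kept in usual care.

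| c | rho | Implied gap | Bias | Per-protocol ANOVA rejections |
|---|---|---|---|---|
| 0.6 | 0 | 0 | 0 | 4.6% |
| 0.6 | 0.1 | 0.21 | 0.08 | 6.7% |
| 0.6 | 0.2 | 0.42 | 0.17 | 13.3% |
| 0.6 | 0.3 | 0.63 | 0.25 | 25.6% |
| 0.8 | 0.2 | 0.46 | 0.09 | 7.2% |
| 0.4 | 0.2 | 0.42 | 0.25 | 22.1% |

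The row at c = 0.6 and rho = 0.2 has a gap inside the assumed 0.3-0.5 range and agrees with the two-arm calculation: 0.4 × 0.42 = 0.17. Across all simulated scenarios, intention-to-treat ANOVA on the same data rejected in 4.4% to 5.9% of runs.

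**The case against.** **The comparator is not spelled out.** The protocol does not say that compliers are compared with all of usual care, and its reference to a level of compliance would also fit an analysis by degree of use within the digital arms. The set's definition may also sit in a statistical analysis plan that is not at hand. This stands in part: the between-arm comparison is the natural reading, since the sentence follows intention-to-treat for three groups, but it is a reading. A missing cut-off is no finding. The arm-specific criterion is a different matter, because no cut-off on modules or app use can make it apply to usual care. A within-arm contrast of compliers and non-compliers would not be randomised either.

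**Bias is not inevitable.** A reader might infer that the analysis must show a benefit. It need not: the bias vanishes if compliance is unrelated to outcome, and its size rests on two assumptions with no anchor in the protocol. This stands.

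**The main inference is protected.** Intention-to-treat is planned for all three groups and nothing gives the per-protocol result confirmatory status. This stands and limits the severity.

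**Module pace.** The website section says "Participants will review one module per week, completing all modules in an organized manner over a two-month period". Ten modules at one per week take 10 weeks, whereas two months are about 8.7 weeks (2 × 30.4 / 7). A reader might infer that someone keeping the weekly pace would be counted as non-compliant. The protocol does not support this: it describes a delivery schedule, leaves access open afterwards, and nowhere makes two months a compliance limit. It is a wording point only.

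**The remedy has its own weakness.** A complier average causal effect assumes that assignment acts only through the measured use. Module discussion at visits, the telephone call reinforcing the intervention group, and use below the threshold all strain this. The objection stands as a caveat, which is why the estimate can only be supportive.

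**Conclusion.** The concern holds as a flaw in a stated secondary method. The named compliance measures exist only in the digital arms and the named between-group tests are unadjusted. On the natural reading, the per-protocol comparison with usual care can therefore show a benefit when there is none. Under the assumptions of 50-60% compliance and a 0.3-0.5 point prognostic gap, the false benefit is 0.12-0.25 A1c points and the type I error about 9-21% instead of 5%. These figures illustrate the risk and do not measure this trial's error. The possible distortion of web versus web + app is not quantified.

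The trial's main conclusion is not threatened as long as it rests on intention-to-treat. The analysis should be changed, but it does not undermine the design.

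**What to change.** Keep intention-to-treat as the basis for inference and say so. In place of the complier comparison, estimate a complier average causal effect for each digital arm versus usual care, with randomised arm as the instrument, baseline A1c and clinic as covariates, and the module or app-use threshold fixed before results are seen. Label it supportive.

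If a per-protocol comparison is kept, adjust or weight it for baseline A1c and baseline predictors of compliance, and label it exploratory.

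Two wording points should be reconciled at the same time:
- The weekly module pace and the two-month period.
- The statement under usual care that "participants will receive reminders through the mobile app and follow-up calls", against the Table 1 footnote that creates users only for the digital groups. If control participants do use the app, the instrumental-variable analysis must allow for it.

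**Cost.** Analysis-plan wording and one standard analysis. Intervals widen: at 60% compliance the standard error is about 1 / 0.6 = 1.7 times that of intention-to-treat. With 108 per arm and before covariate adjustment, that is 1.3 × √(2/108) = 0.177 rising to about 0.295. The exclusion restriction, strained by the reinforcement call, the in-visit discussion and sub-threshold use, should be stated as a limitation.

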**Methods:**

The study is designed as a 12-month randomized controlled trial with three parallel arms: (1) Web-based education, (2) Web-based education + mobile app (diet and exercise plan), (3) Usual care. The total study duration is 12 months with data collection at baseline, 3, 6, 9 and 12 months. We will enroll 408 Mexican adults with T2D, randomized equally across arms. Measurements at baseline, 3, 6, 9, and 12 months include A1c (primary outcome), lipid profile, anthropometry, body composition, quality of life, lifestyle, and physical activity.

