## Methods/design

### Objectives

The primary objective of this clinical trial is to assess changes in A1c when comparing web-only, web + app, and usual care.

The secondary objectives are to evaluate the effect of the intervention on:
Lipid profile [total cholesterol, LDL-c [low-density lipoprotein cholesterol], HDL-c [high-density lipoprotein cholesterol], and triglycerides].Body composition and anthropometric measurements (body fat percentage, body fat mass, weight, BMI [body mass index], and waist circumference).Quality of life (Diabetes 39, validated in the Mexican population).Lifestyle (IMEVID, validated for diabetes population in Mexico).Level of physical activity [IPAQ (International Physical Activity Questionnaire)].

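### The repeated measures ANOVA is worded as a before-after test inside each arm, which cannot estimate the effect of a randomised intervention and can be significant in usual care without one

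*Protocol article*

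**What the plan says.** The Objectives section makes the primary aim a comparison of arms: to "assess changes in A1c when comparing web-only, web + app, and usual care". The Statistical analysis section then lists several analyses.

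- For continuous outcomes: "One-way ANOVA or Kruskal Wallis test will be used to compare the effect on clinical, anthropometric, and biochemical variables between groups".
- For control targets, a chi-square "test will be used to evaluate the effect of the intervention between groups for metabolic control goals".
- For the population: "An intention-to-treat analysis will be performed for the three groups in the clinical trial".
- In addition: "A repeated measures ANOVA test will also be performed to analyze the effect of the intervention in each of the groups".

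The section also plans a per-protocol analysis and an adjusted logistic regression for glycaemic control. It names no group-by-time term and gives no rule for missing values.

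Three other places bear on the point. Selection criteria admits people "with A1c > 7% and < 13" (per cent). The Clinical management section gives all participants a dietary plan, and the usual-care section gives controls diet, diabetes-care and activity advice. The primary measurement under Follow-up and procedures is "A1c (Basal and 12 months"), and Table 1 agrees, whereas the abstract says "Measurements at baseline, 3, 6, 9, and 12 months include A1c (primary outcome").

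**The concern.** The section describes its other comparisons as made between groups, so the different wording of this sentence points to an analysis carried out separately inside each arm. The change in one arm is not an intervention effect. It mixes any true effect with regression to the mean after selection on a high A1c, with secular change, and with whatever all arms receive. The usual-care arm does not get the website or the app, so its change over time cannot measure their effect at all.

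Two errors could follow in the report. A fall that also occurs in controls could be credited to the website or app. And an arm with a significant fall could be contrasted with an arm without one as though that were a comparison of the arms, which it is not.

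**Working it through.** **The plan's own figure.** Under Design and setting, Δ = 0.5, SD = 1.3, two-sided α = 0.05 and power 80% give n = 2 × (1.96 + 0.84)² × 1.3² / 0.5² = 106.0 per group. Then 106 / 0.8 = 132.5, so 133, raised to 136, and 3 × 136 = 408. The plan's figures reproduce, and this point does not affect them. With 20% loss, 136 × 0.8 = 108.8, so about 109 completers per arm.

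**Regression to the mean.** Inputs from the article: entry window 7 < A1c < 13, SD 1.3, 109 completers. Assumptions, because the article gives no figures: source-population mean μ of 7.5, 8.0 or 8.5; correlation ρ between baseline and 12 months of 0.5 to 0.9; normal values; the qualifying A1c is the baseline value; the SD of 1.3 applies to the source population before selection. There is no true change and no treatment effect. With two time points, a repeated measures ANOVA in one arm is the paired test.

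Expected drift = −(1 − ρ) × (mean baseline after selection − μ). For μ = 8.0 the selected mean is 8.49 and the selected SD 0.97. At ρ = 0.5:

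- drift = −0.5 × 0.49 = −0.245;
- SD of change = √(0.5² × 0.97² + 1.3² × (1 − 0.5²)) = √(0.235 + 1.268) = 1.226;
- SE = 1.226 / √109 = 0.117;
- 0.245 / 0.117 = 2.09 against a critical value of 1.98, so the chance of rejection is about Φ(0.11) = 0.54. Simulation gives 0.55.

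Simulated within-arm rejection rates at a nominal 5% (mean drift in brackets):

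| Source mean | ρ = 0.5 | ρ = 0.7 | ρ = 0.9 |
|---|---|---|---|
| 7.5 | 89% (−0.37) | 67% (−0.22) | 27% (−0.07) |
| 8.0 | 55% (−0.25) | 35% (−0.15) | 15% (−0.05) |
| 8.5 | 25% (−0.15) | 16% (−0.09) | 8% (−0.03) |

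With all 136 per arm the range is 9% to 94%. With a source SD of 1.8, which leaves a selected SD of 1.16 to 1.32, it is about 13% to 94% at 109 completers. A between-arm t-test of change on the same data rejects in 4.6% to 5.4% of trials in every scenario.

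**Disagreement between arms with the same true change.** Assume ρ = 0.5 and SD 1.3 at both times. The SD of change is 1.3 × √(2 × (1 − 0.5)) = 1.3, and the SE is 0.125 with 108 or 109 completers. If each arm is significant with probability p, the three arms fail to agree with probability 1 − p³ − (1 − p)³.

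| Common true fall | p | Arms disagree |
|---|---|---|
| 0 | 0.05 | 14% |
| 0.1% | 0.126 | 33% |
| 0.3% | 0.669 | 66% |
| 0.5% | 0.979 | 6% |

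Disagreement is therefore common for small shared falls and rare for large ones. A large shared fall brings the other error instead: all three arms are significant although the arms do not differ.

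**The case against.** The strongest reply is that this test is supplementary. The sentence says it is also performed; the same section plans between-group tests of continuous outcomes and of control targets, and a logistic regression that includes the intervention group. The objective is a comparison of arms and the sample size rests on one. All of that stands. A reader might infer that the trial will judge its intervention only by within-arm p-values, or plans to compare arms by which are significant. The article says neither. What remains is that the sentence calls a within-arm change an intervention effect, and nothing in the section ranks it below the other analyses.

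The authors may also have meant a mixed-design ANOVA with arm as a factor. If so, the group-by-time contrast is the quantity of interest, and the sentence should name it.

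A second tempting inference is that the test contradicts the intention-to-treat statement by deleting incomplete cases. Classical repeated measures ANOVA does drop them by default, but the article states no missing-data rule, and an analysis plan that is not shown may give one. No conflict is shown. Nor would missed visits at 3, 6 or 9 months remove anyone from the A1c analysis on the Table 1 schedule, which has A1c only at baseline and 12 months; they could do so only under the abstract's five-visit description.

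Finally, the size of the problem depends on assumed inputs. That is fair, and is why ranges are given.

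**Conclusion.** The point holds in limited form. As worded, the repeated measures ANOVA has the wrong target: it tests change inside an arm and labels it an effect of the intervention. The between-group tests remain, so the sentence does not invalidate the trial, but it should not stand as written.

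Under the assumptions above, an arm with no true change would show a significant change in about 8% to 89% of trials, against about 5% for a between-arm test. The direction was the same in every scenario tried; the amount was not. It would be smaller if the qualifying A1c were a separate measurement from the baseline value, which the article does not settle. Advice and plans given to all arms could add a real fall in usual care, which the no-change simulation leaves out.

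**What to change.** Replace the sentence so that the intervention effect is the between-arm contrast at 12 months:

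- for A1c, measured at baseline and 12 months in Table 1, ANCOVA of the 12-month value on arm, adjusted for baseline A1c;
- for continuous outcomes measured at several visits, such as weight and waist circumference, a linear mixed model with arm, visit and arm-by-visit terms, reporting the arm contrast at 12 months.

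Report within-arm changes descriptively and do not call them intervention effects. Reconcile the A1c time points in the abstract with Table 1, since they decide which of the two models applies to the primary outcome.

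A side benefit is that a mixed model keeps participants with incomplete visits. The cost is analysis wording and slightly more analysis work; no extra participants, visits or measurements are needed.
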